### 8.1.4. Dose-Limiting Toxicity Criteria

The DLT observation period is defined as 14 days after infusion of agenT-797. The nature, frequency, time to onset, severity of toxicities, medical history, and concomitant medication, as well as the success of standard medical management, will be analyzed to determine if a given toxicity should be considered a DLT by the SMC per charter.

A DLT is defined as any of the following at least possibly related AEs graded using NCI-CTCAE v5.0:

- General:
  - Any Grade 4 or 5 toxicity
- Hematologic:
  - Any Grade 3 hematologic toxicity that lasts for more than 7 days despite treatment

- Non-hematologic:
  - Any Grade 3 non-hematologic toxicity that lasts for more than 72 hours despite adequate treatment
  - Exceptions: Grade 3 events with a different definition of duration that are considered DLTs are the following:
    - Grade 3 renal or hepatic toxicity that lasts 7 days or longer
    - Any Grade 3 or higher toxicity that is cardiac, respiratory, or neurologic of any duration
- Immune:
  - Any Grade 2 acute GVHD that requires steroid therapy for > 7 days or that has progression of clinical signs and symptoms after 3 days of steroids or that has partial response after 14 days of treatment, or GVHD Grade 3 or higher
  - Any **new** Grade 3 CRS lasting more than 72 hours and/or **new** Grade 4 CRS of any duration at least possibly related to agenT-797. For patients presenting with Grade 2 or 3 CRS at baseline, worsening of baseline CRS grade, judged as at least possibly related to agenT-797, and occurring within 4 hours of infusion ([Lee 2019](#))
  - Any clinically significant Grade 3 autoimmune disorder that lasts for more than 72 hours at Grade 3 despite adequate treatment or any Grade 4 autoimmune disorder of any duration

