### 3.6 Dose-Limiting Observation Period

A minimum of 3 patients will be enrolled in each cohort, and the DLT observation period will be 14 days for each patient. Patients will continue to be monitored post-DLT period throughout the study. The totality of the safety data will be factored in by the SMC in the decision-making to move to enrollment of Cohort 2.

If a DLT occurs in 1 of the 3 patients during the DLT period, the cohort will be expanded to a total of 6 patients; if a DLT occurs in  $\geq 2$  patients in the total cohort of 6 patients, the MTD will be deemed to be exceeded, and that dose will not be escalated. The prior dose level will be evaluated to then proceed into the Expansion Cohort. The interval between patients in each cohort is at least 7 days with a 14-day interval between each cohort (Section 1.3).

The dose of agenT-797 will be escalated if none of the first 3 evaluable patients enrolled has a DLT based on SMC evaluations of data. If a cohort was expanded to include a total of 6 evaluable patients and no DLT occurs in the additional 3 patients, then the dose will be escalated based on the SMC evaluation of data.

After Amendment 7, the SMC will monitor safety on an ongoing basis.

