### 3.8 Safety Criteria for Adjustment or Stopping Doses

Enrollment and treatment will be temporarily stopped if any of the following occur:

- DLT(s) defined as follows: two Grade 4 DLTs or single Grade 4 neurological toxicity or single Grade 3 or higher Graft-versus-Host Disease (GVHD) as DLT
- Any toxicity that is unexpected, significant, and unacceptable (based on SMC review and discussion), e.g., any occurrence of GVHD Grade 3 or higher

- Any death that occurs within 30 days of agenT-797 administration, except cases reported as related to the primary disease (COVID-19 or influenza)

If any of the above stopping criteria are met, an SMC meeting will occur to review the information and to recommend how to proceed.

The SMC will review any cohort under evaluation as well as the safety of all cohorts. All toxicities, including those outside the 14-day DLT period, will be evaluated.

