### **3.9 Treatment and Evaluation Period**

Eligible patients will be treated with agenT-797 on Day 1. Assessments will be obtained through Day 32 or until discharge from hospital as outlined in the Schedule of Assessments in Table 3 of the study protocol.

After the patient has received a single infusion of agenT-797, the EOH is defined as patient discharge from the hospital or death.

The Safety Follow-up period will be 30 days, and the patient will be contacted by telephone 3 and 6 months after discharge regarding any SAEs and to confirm survival, as feasible. The first Safety Follow-up Visit will be at Day 30 ( $\pm 2$ ), or at EOH. If a patient is discharged at Day 30, 30-day Follow-up will be the same as EOH.

Patients are at any time free to withdraw from the study. Such patients will always be asked about the reason(s) and the presence of any AEs. The Investigator may also elect to discontinue patients from the study, for example, to pursue a different treatment option. Reason(s) for discontinuation will be documented.

Patients who are withdrawn from the study but have completed treatment (infusion of agenT-797), are to be considered evaluable for DLT, and will not be replaced. Any patient who is withdrawn and is not considered evaluable for safety during Dose Escalation will be replaced to ensure a minimum number of evaluable patients.

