### 4.5 Analysis Sets

Three subject analysis sets are defined for the study analyses, as follows:

- **The All Subject Analysis Set** will include all patients who have completed informed consent, irrespective of the study treatment administered. This analysis set will be used for the disposition summary and the listing of study populations.
- **The Safety Analysis Set** will include all patients who received agenT-797. This analysis dataset will be used for safety analysis and all listings other than listings of subject disposition and study populations.
- **The Dose-Limiting Toxicity Analysis Set** will include all patients who either experienced a DLT within 28-day observation or completed study treatment and 28-

day observation for DLT without experiencing DLT. The DLT analysis set will be used for the analysis of DLT rates and for determining MTD.

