### **4.11.3 Safety Evaluation**

The DLT analysis set will be used for the DLT rate and MTD of agentT-797. The safety analysis set will be used for all other safety analyses.

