| D-dimer, CPK, cardiac troponins, and ferritin                                         |                | Every 12h, as feasible                 |   |   |   |   |        |                     |                     |                     |                        | X                |            |

Abbreviations: AE: adverse events; AESI: adverse events of special interest; ARDS: acute respiratory distress syndrome; d: day(s); cfDNA: cell free DNA; CPK: creatine phosphokinase; CT: computed tomography; ECG: electrocardiogram; EOH: End-of-Hospitalization; F/U: Follow-up; HLA: human leukocyte antigen; h: hour (s); IL: interleukin; iNKT cells: invariant natural killer T cells; RT-PCR: reverse transcriptase polymerase chain reaction; SAE: serious adverse event; SOFA: sequential organ failure assessment; WOCBP: women of childbearing potential.

a End-of-Hospitalization is defined as patient discharge from hospital and/or death. If a patient is discharged at Day 30, 30-day Follow-up will be the same as EOH. After discharge, a patient will enter Safety Follow-up period and the patient will be contacted by telephone 3 and 6 months after discharge regarding any SAEs and to confirm survival, as feasible..

b In case of earlier discharge from the hospital, no visit is expected until 30-Day Follow-up.

c Performed before infusion of agenT-797 on D1. These samples will be obtained at the time of the routine labs blood draws.

d A complete examination, as feasible, will be performed at Screening and symptom-directed and medically indicated physical examinations are done thereafter.

e Vital signs include body temperature, heart rate, respiratory rate, systolic and diastolic blood pressure and are assessed by physician or nurse. On the day of infusion of agenT-797 (D1), measurements will be 15 min prior to infusion, and 15 min, 30 min, 1h, 2h, 3h, and 4h postinfusion.

- f ECG to be performed at Screening, Day 1 predose and EOH, 30-Day Follow-up, and at other times as clinically indicated.
- g Only AEs associated with study procedures and/or leading to withdrawal and all SAEs will be collected prior to study drug infusion. Patients are monitored for toxicities following infusion. All other AEs, SAEs, and AESIs will be collected in the Safety Follow-up period.

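### The SAP builds the DLT Analysis Set on a 28-day window, while every other statement in the protocol and the SAP gives 14 days, so the denominator of the DLT rate and the basis for the MTD are not consistently defined

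*Combined protocol and SAP*

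**What the plan says.** SAP 4.5 admits a patient to the DLT Analysis Set in one of two ways. The set "will include all patients who either experienced a DLT within 28-day observation or completed study treatment", and the second route also requires 28 days of observation without a DLT. The figure 28 therefore stands in both routes. On the use of the set, SAP 4.5 states: "The DLT analysis set will be used for the analysis of DLT rates and for determining MTD". SAP 4.11.3 says the same. SAP 4.11.6 builds the DLT tables on this set and counts events in a DLT evaluation period whose length it does not give.

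All other statements of the window are 14 days:

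- SAP 3.6, protocol 4.5.1 and the protocol synopsis: "the DLT observation period will be 14 days for each patient".
- Protocol 8.1.4, the DLT definition: "The DLT observation period is defined as 14 days after infusion of agenT-797".
- SAP 3.8 and protocol 4.5.3: "All toxicities, including those outside the 14-day DLT period, will be evaluated".

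On evaluability, SAP 3.9 and protocol 4.11 say that patients withdrawn after a completed infusion "are to be considered evaluable for DLT, and will not be replaced". DLTs are part of the primary endpoint (protocol section 3, SAP Table 2).

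**The concern.** A programmer who follows SAP 4.5 would apply a window that nothing else in the two documents uses. Three things follow.

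- A patient who completed the 14-day period without a DLT is removed if death from the underlying disease or withdrawal comes before Day 28.
- Patients withdrawn after infusion are removed, against the SAP's own rule in 3.9.
- Events on Days 15 to 28 may be counted as DLTs, depending on what the evaluation period in SAP 4.11.6 means.

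At stake are the DLT proportion by dose level, which belongs to the primary endpoint, and the stated basis for the MTD. Cohorts are small and the patients are critically ill, so a few exclusions change the reported figures visibly.

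**Working it through.** **Inputs.** Windows of 28 days (SAP 4.5) and 14 days (SAP 3.6 and 3.8; protocol synopsis, 4.5.1, 4.5.3 and 8.1.4). At least 7 days between patients and 14 days between cohorts (protocol 4.5.1, SAP 3.6). Cohorts of 3, expanding to 6. A DLT must be at least possibly related (protocol 8.1.4). No imputation (SAP 4.11.1.1). Wilson intervals (SAP 4.2).

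**The plan's own figure.** The window is a definition and cannot be recomputed. The DLT-design number that can be checked is the Part 1 maximum: 3 dose levels × 6 = 18, as stated in protocol 9.2.

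**Which window the staggering fits.** With n patients dosed 7 days apart and the next cohort opening 14 days after the last, patient i has 14 + 7(n − i) days of follow-up at the earliest opening.

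| Cohort size | Days of follow-up | Completed 14 days | Completed 28 days |
|---|---|---|---|
| 3 | 28, 21, 14 | 3 of 3 | 1 of 3 |
| 6 | 49, 42, 35, 28, 21, 14 | 6 of 6 | 4 of 6 |

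**Who is in the set.**

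| DLT-free patient who | SAP 4.5 as written | Same clause with 14 days | SAP 3.9 / protocol 4.11 |
|---|---|---|---|
| is observed to Day 28 | in | in | no conflict |
| completes 14 days, withdraws before Day 28 | out | in | evaluable |
| completes 14 days, dies unrelated before Day 28 | out | in | deaths not mentioned |
| withdraws after infusion, before Day 14 | out | out | evaluable |
| dies unrelated before Day 14 | out | out | deaths not mentioned |

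**Denominator effect, 6 treated.** The rate is x/(6 − lost). With p = x/n and z = 1.96, the Wilson limits are [p + z²/(2n) ± z√(p(1 − p)/n + z²/(4n²))] / (1 + z²/n).

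| DLT-free patients lost | 1 DLT: rate (95% CI) | 0 DLTs: upper limit |
|---|---|---|
| 0 | 1/6 = 16.7% (3.0 to 56.4) | 39.0% |
| 1 | 1/5 = 20.0% (3.6 to 62.4) | 43.4% |
| 2 | 1/4 = 25.0% (4.6 to 69.9) | 49.0% |

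**How often this would happen.** Let L be the probability of death or withdrawal without a DLT by Day 28. The documents give no such figure, so 10% to 40% is an assumed range. For 6 patients, the chance of losing at least one under a 28-day completion rule is 1 − (1 − L)⁶. At constant hazard the 14-day loss is 1 − (1 − L)^½, so the chance under a 14-day rule is 1 − (1 − L)³.

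| L | 28-day rule | 14-day rule |
|---|---|---|
| 10% | 46.9% | 27.1% |
| 20% | 73.8% | 48.8% |
| 30% | 88.2% | 65.7% |
| 40% | 95.3% | 78.4% |

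**Numerator effect, only if Days 15 to 28 count.** With an assumed 14-day DLT probability p and constant hazard, the 28-day probability is 1 − (1 − p)²: 10%, 20% and 30% become 19%, 36% and 51%. If the hazard halves after Day 14, 1 − (1 − p)^1.5 gives 14.6%, 28.4% and 41.4%.

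**The case against.** The strongest reply is that little depends on this. Part 1 is marked completed, escalation was decided by the SMC under design text that says 14 days, all analyses are descriptive, and AEs, severity and deaths are reported on the Safety Analysis Set. SAP 4.5 also does not redefine a DLT. If the evaluation period in SAP 4.11.6 is the 14 days of protocol 8.1.4, the numerator does not change. All of this stands, and it limits the point to the DLT rate and any MTD taken from this set. It does not remove the contradiction, because SAP 4.5 names exactly those two uses.

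Several stronger readings are tempting but not supported:

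- **That the DLT rate must be inflated.** Removing DLT-free patients raises the proportion arithmetically, but an early death can also prevent a later DLT from being seen. The net direction of bias is uncertain. A death at least possibly related to agenT-797 is itself a DLT, and that patient stays in the set.
- **That the death proportions in Table S1 (2 of 5 and 17 of 35) measure the loss.** They concern VV-ECMO patients only and carry no time point. They also cannot separate deaths before Day 14, which a 14-day completion clause would drop as well.
- **That early discharge makes 28 days unobservable.** The schedule says: "In case of earlier discharge from the hospital, no visit is expected until 30-Day Follow-up". The same footnote is attached to the Day 14 visit, so it does not distinguish the two windows. AEs are collected continuously, and a Day 30 follow-up exists.
- **That changing 28 to 14 settles the matter.** The table of patient types shows that patients who die or withdraw before Day 14 would still be dropped. The evaluability rule addresses withdrawal and does not mention death, which protocol 4.9 treats as End-of-Hospitalization.

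**Conclusion.** The point holds as a contradiction in current text. One section of the SAP uses 28 days where the rest of both documents uses 14, and that section governs a primary-endpoint rate and the stated basis for the MTD. The 28-day figure is called inconsistent here because nothing else in the documents matches it and the between-cohort interval fits 14 days. Which window is clinically appropriate is not for this review to say.

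The arithmetic for 6 treated patients needs no assumption beyond the number lost. The probabilities of loss rest on the assumed 10% to 40% and a constant hazard. The gap between their two columns, not the 28-day column alone, is what the window contributes. A reader might infer that doses were escalated wrongly in Part 1; the documents do not show that any escalation decision used the 28-day set.

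**What to change.** Amend the SAP before the DLT tables are produced:

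1. Reconcile SAP 4.5 with SAP 3.6 and 3.8 and protocol 4.5.1 and 8.1.4, so that one stated window defines both the set and the evaluation period in SAP 4.11.6. If 28 days is intended, the 14-day statements and the 14-day between-cohort interval have to be reconciled with it, which needs a protocol change as well.
2. Align the completion clause with the evaluability rule in SAP 3.9 and protocol 4.11, and state how deaths without a DLT inside the window count.
3. Report the DLT proportion on all infused patients next to the one on the DLT set. Protocol 9.1 already places all safety analyses on the Safety Analysis Set.
4. List infused patients who are not DLT-evaluable, with the reason.
5. Tabulate toxicities after the DLT window separately.

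Unless the 28-day window is kept, the cost is SAP wording, one extra table column, a listing and a late-toxicity table. No new data are needed.

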#### 4.6 Demographics and Baseline Characteristics

Demographic and baseline characteristics will include age, sex, race, ethnicity, height, weight, body mass index (BMI) and serum pregnancy test results for all women of childbearing potential based on the safety set, by dose group and overall.

Age will be derived from patients' date of birth as the number of complete years between a subject's birth date and the date of informed consent.

Summary tables will be presented for both continuous variables (age, height, weight and BMI) and categorical variables (sex, race, ethnicity and serum pregnancy test results) using frequency and percentages.

A by-subject listing of the demographics and baseline characteristics will be provided.

#### 4.7 Diagnosis and Extent of Disease

Summary statistics will be tabulated for the diagnosis and extent of the disease based on the safety set, by dose group, and overall. This analysis will include the following:

- Time since initial diagnosis
- Peripheral blood sample tests at study entry
- Urine sample tests at study entry

A by-subject listing of the diagnosis and extent of the disease will be provided.

#### 4.8 Medical History and Concomitant Illnesses

All medical history, concomitant conditions and symptoms entered on the electronic case report form (eCRF) will be coded by system organ class (SOC) and preferred term (PT) using the Medical Dictionary for Regulatory Activities (MedDRA) version 22.0 or higher based on the safety analysis set.

All medical history and concomitant illnesses will be listed by subject.

#### 4.9 Prior and Concomitant Medications

All prior and concomitant medications will be based on the safety set.

Medication start and stop dates will be compared to the date of first dose of study medication to allow medications to be classified as either prior only, both prior and concomitant, or concomitant only. Medications starting after the completion/withdrawal date will be listed but will not be classified or summarized.

Medications that start and stop prior to the date of first dose of study medication will be classified as prior only. If a medication starts before the date of first dose of study medication and stops on or after the date of first dose of study medication, then the medication will be classified as both prior and concomitant. Medications will be classified as concomitant only if they have a start date on or after the date of first dose of study medication.

If medication start and/or stop dates are missing or partial, the dates will be compared as far as possible with the date of first dose of study medication. Medications will be assumed to be concomitant only, unless there is clear evidence (through comparison of partial dates) to suggest that the medication started prior to the first dose of study medication. If there is clear

evidence to suggest that the medication started prior to the first dose of study medication, the medication will be assumed to be both prior and concomitant, unless there is clear evidence to suggest that the medication stopped prior to the first dose of study medication. If there is clear evidence to suggest that the medication stopped prior to the first dose of study medication, the medication will be assumed to be prior only.

A by-subject listing will be listed for each patient.

## **4.10 Treatment Exposure / Compliance**

### **4.10.1 Treatment Exposure**

AgenT-797 will be administered as a single intravenous infusion of allogeneic iNKT cells over 10 to 30 minutes on Day 1. The extent of the exposure to agenT-797 will be summarized and presented based on the safety analysis set, by dose level and overall. The summary will include:

- Duration of agenT-797 administration, defined as the number of minutes between the administration start time and the end time
- Calculated dose level
- Actual dose level

A by-subject listing of exposure data will be provided.

### **4.10.2 Compliance**

AgenT-797 should only be used as directed in this protocol and as detailed in the Pharmacy Manual. Details of treatment with agenT-797 for each subject will be recorded in the eCRF.

## **4.11 Efficacy Evaluation**

### **4.11.1 Analysis and Data Conventions**

No formal testing of hypotheses has been planned in this study. All analyses will be based on descriptive statistics.

#### **4.11.1.1 Handling of Dropouts or Missing Data**

No imputation will be made for missing data resulting from an early withdrawal, missed evaluations, or any other unforeseen reason. All missing or partial data will be presented in the patient data listings as they are recorded on the eCRF.

#### **4.11.1.2 Interim Analyses**

Interim analyses may be performed as appropriate and will be informal, descriptive and exploratory in nature, without any formal statistical testing.

### **4.11.2 Efficacy Variables**

The analysis of clinical activity will be performed on the safety analysis set.

The following clinical responses will be investigated.

#### **4.11.2.1 Intubation/continuation/discontinuation of intubation/mechanical ventilation**

The time between dose and intubation, time of continuation and then time between dose and extubation can be used to measure the efficacy of the therapy.

The following parameters will be computed together with their 95% CI:

- Median time between dose and intubation
- Median time between dose and extubation
- Medium intubation continuation time

#### **4.11.2.2 Supportive oxygenation intervention**

The length of time of oxygenation intervention is a good indication of efficacy. The median time for oxygenation intervention will be computed.

#### **4.11.2.3 Baseline and every 12 hours as feasible: C-reactive protein, D-dimers, ferritin, IL-1, IL-6 to assess CRS evolution**

A longitudinal analysis of all these biomarkers will be done to assess CRS evolution. Longitudinal plots for these variables for each patient will be provided.

#### **4.11.2.4 All-case mortality**

Proportion of death from all causes within 30 days and at 6 months and its 95% score CI will be calculated. It is a direct measurement of efficacy of the therapy.

